### Sample size

In the data published by Wang et al. [34] to evaluate an intervention in stable COPD patients, a weighted common standard deviation of the CAT score of 5.69 was observed. Basing the sample calculation on these data, in a study of the superiority of montelukast compared to placebo with an intention-to-treat analysis, accepting an alpha risk of 0.05 and a beta risk under 0.2 in a two-tailed contrast, 142 individuals in the treatment group and 142 in the control group are needed to detect a difference of 2 units. We assume a 10% loss to follow-up rate.

### Recruitment

Potential participants will be identified by the collaborator investigators at primary health centers and contacted in office visits or by telephone. If participants with persistent respiratory symptoms score from 1 to 3 (mild to moderate) dyspnea according to the modified Medical Research Council scale (mMRC) [35] and they agree to participate, an appointment will be scheduled with a physician investigator to assess the eligibility and to sign the informed consent. The recruitment period is estimated to finish by May 2022 or when a sufficient sample size is reached.

### Randomization, allocation, implementation, and blinding process

Participants will be randomly allocated to the intervention (treatment) or control (placebo) group. The randomization will be carried out by a IDIAPJGol statistician not involved in the recruitment using the R statistical software to obtain computer-generated random numbers without stratification, in a 1:1 allocation ratio by blocks of 4. The distribution will be made by blocks to ensure the proportionality of treatments between centers.

The randomization list will be provided to the pharmacy, which will label the trial treatments accordingly. Each treatment will be identified with a unique code. The centers will have medication in sequential order. The medication code dispensed to the patient will be registered on the medication dispensing form and on the data collection logbook. Since this is a double-blind study, neither healthcare professionals, patients nor the research team will be aware of the allocated group. Montelukast pills and their placebo equivalent will be visually identical.

Unblinding of a participant’s treatment will be allowed when information of the treatment received is needed for the effective and secure management of the patient.

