### Study setting

The study will be carried out in thirteen primary healthcare centers in four health areas of Catalonia and Aragon, Spain. The list of study sites can be found at the Spanish Clinical Studies Registry website (https://reec.aemps.es).

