### Statistical analysis

Baseline characteristics of the sample will be described for each group using mean and standard deviation for quantitative variables and absolute and relative frequencies for qualitative variables. Bivariate comparison of characteristics between patients taking montelukast and patients taking placebo will be carried out to verify group comparability. The Wilcoxon test will be used for the comparison of quantitative variables and the chi-square test for the comparison of qualitative variables (or the Fisher test in case of extreme distributions in the crossed tables). In all comparisons, the statistical significance will be set at 5%.

Outcome measures will be described and compared between the montelukast and placebo groups using the same statistics. No multivariate analysis will be performed.

For the primary endpoint analysis (montelukast efficacy) and secondary endpoints, we will primarily use an intention-to-treat analysis. We will also conduct a per-protocol analysis. R-4.0.2 for Windows will be used.

Additional subgroup analysis will be performed based on symptom duration (< 6 months and ≥ 6 months).

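### Blocks of 4 handed out by center balance the arms within center, but the fixed analysis ignores center; if centers differ, the test is mildly conservative

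*Protocol article*

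**What the plan says.** In the protocol article, the section on randomization, allocation, implementation and blinding says the list comes from "computer-generated random numbers without stratification, in a 1:1 allocation ratio by blocks of 4". The next sentence reads: "The distribution will be made by blocks to ensure the proportionality of treatments between centers". The same section has each center dispensing its numbered medication in sequence.

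Study setting gives the number of sites: "The study will be carried out in thirteen primary healthcare centers". They lie in four health areas.

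Statistical analysis names the Wilcoxon test for quantitative variables and applies the same tests to the outcomes. It closes the matter with "No multivariate analysis will be performed". No stratified rank test is named.

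**The concern.** A block of 4 holds two patients per arm. If whole blocks go to a center and are used in order, the arms there are balanced except for an incomplete last block. Center is then a design factor, whatever label the list carries, and a reader of the article cannot tell whether it should be treated as one.

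With arms balanced within center, differences between centers cancel out of the treatment contrast. An unadjusted test still counts them as random error. Its variance estimate is too large, its actual type I error lies below the nominal 5%, and it misses a gain in power that the design has made available. For the planned test, this variance is the null variance of the Wilcoxon statistic.

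This is not a detail left to an unseen analysis plan, because the article itself rules out a model with a center term.

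**Working it through.** **Inputs from the Sample size section.**
- Error rates: two-sided alpha 0.05, power at least 80%.
- Spread: "a weighted common standard deviation of the CAT score of 5.69 was observed".
- Target difference and size: 2 CAT points, 142 per arm.
- Attrition: 10%.

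**Assumed input.** The ICC of CAT between centers is in neither the sample size nor any other section. The range shown is 0 to 0.20, with the total SD held at 5.69.

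**Step 1: the plan's own figure.** n per arm = 2 × [5.69 × (1.960 + 0.842) / 2]² = 127.06, or 128 rounded up. Allowing for 10% loss, 127.06 / 0.9 = 141.2, rounded up to 142. The stated 142 is reproduced (rounding to 128 first gives 143). 284 / 13 is about 22 patients randomized per center.

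**Step 2: formulas, at 128 evaluable per arm.**
- Unadjusted SE = 5.69 × √(2/128) = 0.711.
- Actual SE with arms balanced within center = 0.711 × √(1 − ICC).
- Actual type I error of the unadjusted test = 2 × [1 − Φ(1.96 / √(1 − ICC))].
- Power, unadjusted = Φ[(2/0.711 − 1.96) / √(1 − ICC)].
- Power, center-adjusted = Φ[2 / (0.711 × √(1 − ICC)) − 1.96].

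Example at ICC 0.10, where √0.9 = 0.949:
- Actual SE = 0.675.
- Type I error = 2 × [1 − Φ(2.066)] = 0.039.
- Unadjusted power = Φ(0.898) = 81.5%.
- Adjusted power = Φ(1.004) = 84.2%.

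| ICC (assumed) | Actual SE | Unadjusted SE too large by | Actual type I error | Power, unadjusted | Power, adjusted |
|---|---|---|---|---|---|
| 0 | 0.711 | 0% | 0.050 | 80.3% | 80.3% |
| 0.02 | 0.704 | 1.0% | 0.048 | 80.5% | 81.1% |
| 0.05 | 0.693 | 2.6% | 0.044 | 80.9% | 82.3% |
| 0.10 | 0.675 | 5.4% | 0.039 | 81.5% | 84.2% |
| 0.20 | 0.636 | 11.8% | 0.028 | 83.0% | 88.2% |

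**Step 3: simulation of the planned test.** 13 centers of 19 or 20, 256 patients, blocks of 4 within center, 2,000 runs per scenario.

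| ICC (assumed) | Type I error, plain Wilcoxon | Power, plain Wilcoxon | Power, van Elteren |
|---|---|---|---|
| 0 | 0.045 | 78.5% | 77.3% |
| 0.02 | 0.049 | 77.5% | 76.3% |
| 0.05 | 0.046 | 78.9% | 78.8% |
| 0.10 | 0.038 | 77.2% | 79.2% |
| 0.20 | 0.030 | 82.1% | 85.8% |

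Van Elteren's type I error stayed at 0.044 to 0.056. As a control, the blocks were then not tied to center. The plain Wilcoxon now held 0.047 to 0.055 at every ICC, so the conservatism comes from the balance within center.

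**Step 4: separating center from the choice of test.** A second simulation used 13 centers of 20 and 3,000 runs. At ICC 0 power was 79.5% for Wilcoxon, 81.5% for a plain t-test and 81.7% for a center-adjusted linear model. About 2 points therefore come from replacing ranks by means on normal data, not from center. At ICC 0.05 the figures were 80.6%, 82.3% and 83.6%, so center adds 1.3 points. At ICC 0.10 and 0.20 center adds about 3 and 4.5 points. The formula in step 2 gives 2.7 and 5.2, which agrees within the precision of the simulation.

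**The case against.** **Blocking within center is an inference.** One list cut into whole blocks and shipped to centers would fit both sentences of the randomization section, and the article does not say how blocks were assigned. The full protocol may. This stands as a limit on certainty. But balance across centers is the declared purpose, and blocks used in sequence deliver it within each center under either description.

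**The size depends on an ICC that the documents do not give.** At 0.05 or less the effect is negligible. The eligibility criteria narrow the case mix (mMRC 1 to 3, no hospital admission for the infection, no chronic respiratory disease), and the CAT is completed by the patient, which weakens an argument from assessor differences. This stands too.

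**The error is on the safe side.** A reader might infer that the mismatch invalidates the test or inflates false positives. It does neither: the actual level is at or below 5%, and the contrast is unbiased. Nor is the trial too small on this account. The 142 per arm is reproduced, and by the formula the power of the unadjusted test rises slightly with the ICC. What is lost is an available gain, not planned power.

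**Two tempting overstatements.** Comparing a plain Wilcoxon test with a center-adjusted linear model credits center with about 2 points that belong to the switch from ranks to means. And adjustment is not free in every form: van Elteren lost 1.2 points at ICC 0 and at 0.02 in one simulation, and 1.6 (77.9% v 79.5%) and 1.4 (78.8% v 80.2%) in the other.

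**Conclusion.** The point holds as a modest mismatch between design and analysis. The allocation in effect blocks by center, the list is described as unstratified, and the fixed analysis leaves center out. If centers differ, the planned test is mildly conservative, with an actual level of about 4.5% at ICC 0.05 and 3 to 4% at 0.10 to 0.20. A center term in a linear analysis would add about 1, 3 and 4.5 points of power at ICC 0.05, 0.10 and 0.20, and nothing at 0. These figures rest on an assumed ICC, on the plan's SD of 5.69 and difference of 2, on centers of similar size, and on the reading that whole blocks are allotted to centers. The documents support neither a claim of bias or false-positive inflation nor one of an inadequate sample size. The change is worth making because it is cheap and planned power is only about 80%.

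**What to change.** 1. In the randomization section, state that blocks are allotted by center, and remove or explain the unstratified label.
2. In Statistical analysis, replace the sentence that rules out modeling with a primary linear model for CAT at 4 weeks that contains treatment and center. The cost is up to 12 degrees of freedom. With 256 evaluable patients, 256 − 1 − 1 − 12 = 242 remain for error.
3. If a rank test is kept, use the center-stratified van Elteren test and accept a loss of about 1 to 1.5 points of power when center effects are near zero.
4. At the least, prespecify a center-adjusted sensitivity analysis.

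No patients, visits or data are added beyond recording the center. The change should be made before unblinding, so that adding center cannot look data-driven.

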### Intervention

The intervention consists of a 28-day treatment, with oral administration of 1 capsule per day (research drug or placebo). Participants belonging to the:
Intervention group will be treated with montelukast 10 mgControl group will receive the placebo (microcrystalline cellulose)

The Pharmacy Department of Bellvitge University Hospital will encapsulate montelukast and the placebo.

Follow-up consists of a series of office visits (days 1, 14, and 28) and telephone visits (days 7, 21 and 56), as described in Fig. 1 and Table 2. A window period of ± 2 days for each visit will be accepted.

**Fig. 1 Fig1:**
[figure not shown]
Summary and steps for the E-COVID study. IC, informed consent; CAT, COPD Assessment Test; PCFS, Post-COVID-19 Functional Status Scale; 1MSTS, 1-min sit-to-stand test

**Table 2 Tab2:** Time schedule of recruitment, enrollment, intervention, assessments, and visits

	Study period							
	Enrollment	Allocation	Post-allocation					Close-out
Time point**	***t***_***0***_	***0***	***t***_***1***_	***t***_***2***_*******	***t***_***3***_	***t***_***4***_*******	***t***_***5***_	***t***_***f***_*******
**Enrollment**								
**Eligibility screen**	X	X						
**Informed consent**		X						
**Allocation**		X						
**Interventions**								
**Intervention [montelukast]**								
**Control [placebo]**								
**Assessments**								
**CAT scale**	X		X	X	X	X	X	X
**PCF Scale**			X	X	X	X	X	X
**1MSTS test**			X		X		X	
**Severity of symptoms**			X	X	X	X	X	X
**Health services use**				X	X	X	X	X
**Mortality**				X	X	X	X	X
**Sick leave days**							X	
**Side effects and concomitant medication**				X	X	X	X	X
**Treatment compliance**				X	X	X	X	

*Phone call visits

#### Inclusion visit (day 1)

Investigators will collect the following baseline information: sociodemographic data, clinical data, use of concomitant medication, health-related quality of life associated with respiratory symptoms, functional status post-COVID-19, and scoring of asthenia, headache, mental confusion, ageusia, and anosmia.

Participants will perform the 1MSTS test to evaluate the degree of dyspnea on exertion and oxygen desaturation.

A baseline blood test will be performed, including complete blood count, electrolytes, kidney function, liver function, C-reactive protein, creatine kinase, ferritin, d-dimer, type B natriuretic peptide, antinuclear antibodies, lupus anticoagulant, and quantitative anti-SARS-CoV-2 antibodies.

Patients will receive a bottle with the medication (montelukast or placebo), and an appointment for the next visit (on day 7) will be scheduled.

The patient will be asked to return the bottle with the study medication at the end of the study.

#### Office visit (days 14 and 28)

Evaluation of symptoms, treatment adherence, 1MSTS test and oxygen desaturation, and hospitalization since the previous visit will be assessed, as well as the use of concomitant medication, evaluation of adverse events, and compliance with study medication.

#### Phone call (days 7, 21, and 56)

Health-related quality of life associated with respiratory symptoms, post-COVID-19 functional impairment, and symptom progression will be evaluated by means of a telephone call using the same questionnaires. Information regarding the number of visits to the health center, primary and/or hospital emergency care, and hospitalization since the previous visit will be assessed, as well as the use of concomitant medication, evaluation of adverse events, and compliance with study medication.

#### Visit 5 (day 28)

Visit 5 is the last office visit and end of treatment. Patients will be asked to return the bottle with the study medication, and treatment compliance will be evaluated. We will administer the same questionnaires and collect the same data of previous visits.

Relevant concomitant care and interventions are permitted during the trial, with the exception of antileukotriene use.

### Data collection, data management, and quality assurance procedures

Study data will be collected and managed using REDCap, hosted at the Institut Universitari de Recerca en Atenció Primària Jordi Gol i Gurina (IDIAPJGol). REDCap (Research Electronic Data Capture) is a secure, web-based software platform designed to support data capture for research studies, providing (1) an interface for validated data capture, (2) audit trails for tracking data manipulation and export procedures, (3) automated export procedures to common statistical packages, and (4) procedures for data integration and interoperability with external sources [36, 37].

Only the principal investigator or those who have permission can access the data.

A risk approach monitoring plan will be developed and followed via periodic on-site/online visits. Investigators will be instructed in Good Clinical Practice and specific standard operational procedures for the trial.

### Statistical analysis

Baseline characteristics of the sample will be described for each group using mean and standard deviation for quantitative variables and absolute and relative frequencies for qualitative variables. Bivariate comparison of characteristics between patients taking montelukast and patients taking placebo will be carried out to verify group comparability. The Wilcoxon test will be used for the comparison of quantitative variables and the chi-square test for the comparison of qualitative variables (or the Fisher test in case of extreme distributions in the crossed tables). In all comparisons, the statistical significance will be set at 5%.

Outcome measures will be described and compared between the montelukast and placebo groups using the same statistics. No multivariate analysis will be performed.

For the primary endpoint analysis (montelukast efficacy) and secondary endpoints, we will primarily use an intention-to-treat analysis. We will also conduct a per-protocol analysis. R-4.0.2 for Windows will be used.

Additional subgroup analysis will be performed based on symptom duration (< 6 months and ≥ 6 months).

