### Outcomes

The primary outcome is health-related quality of life associated with respiratory symptoms according to the CAT Scale [29] 4 weeks after starting the treatment. CAT is a validated scale to quantify and monitor the impact of COPD on well-being and daily life. It consists of 8 questions (rated from 0 to 5 points) and a total score of 0–40 (0–9 mild, 10–20 moderate, 21–30 severe, and 31–40 very severe). A difference of 2 or more points in health status is considered clinically significant [30].

The following are the secondary outcomes:
Exercise capacity will be measured as the number of repetitions performed in the 1-min sit-to-stand test (1MSTS) [31], which consists of sitting down and getting up from a chair with no hand support as many times as possible for 1 min while connected to a saturation monitor. Measurements include the number of repetitions and oxygen saturation before and after performing the exercise.The Post-COVID-19 Functional Status Scale (PCFS) [32] focuses on relevant aspects of daily life during post-infection follow-up. The scale is intended to help health professionals become aware of functional limitations and to determine the degree of disability.Severity of common symptoms of patients with long COVID will be evaluated using Likert scales [33] [0 (less severe) to 10 (most severe)]: asthenia, headache, mental confusion (brain fog), ageusia, and anosmia.Use of health services, counting number of visits: virtual, primary care center, emergency room, and hospital admissions.Mortality.Sick leave days at day 28 (end-of-treatment).Side effects of the drug occurring at any time of the study period will be assessed and recorded in the data collection platform eCRF.Treatment compliance (percentage of pills taken at the end of treatment) will be estimated at the end of treatment by counting the remaining pills in the bottle or, if not possible, by directly asking the patient.

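### The trial is sized on a 2-point difference in mean CAT, but the primary comparison is a Wilcoxon p-value with no between-group estimate or interval named

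*Protocol article*

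**What the plan says.** All references are to the protocol article.

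- **Outcomes.** The primary outcome is the CAT score "4 weeks after starting the treatment". It is a sum of 8 items and runs from 0 to 40. On relevance: "A difference of 2 or more points in health status is considered clinically significant".
- **Sample size.** The inputs are a CAT standard deviation ("a weighted common standard deviation of the CAT score of 5.69 was observed"), the error rates ("accepting an alpha risk of 0.05 and a beta risk under 0.2 in a two-tailed contrast") and attrition ("We assume a 10% loss to follow-up rate"). The result: "142 individuals in the treatment group and 142 in the control group are needed to detect a difference of 2 units".
- **Statistical analysis.** Quantitative variables are summarised by mean and SD. For the comparison between arms: "The Wilcoxon test will be used for the comparison of quantitative variables". This is set out for the baseline table. The section then says that outcomes are described and compared with those same statistics, and that there will be no multivariate analysis. Intention-to-treat is the main approach, with a per-protocol analysis in addition. The section names no between-group difference, location shift or confidence interval.

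**The concern.** The design question and the declared analysis concern different quantities. The sample size and the relevance threshold are both in CAT points and concern a difference between arms. The declared test asks whether scores in one arm tend to be lower than in the other, and its p-value carries no CAT unit.

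Two things are at stake. First, a significant p-value would not say whether the benefit is near 2 points, well below it or well above it, and a non-significant one would not say whether 2 points has been ruled out. Second, if the two score distributions differ in shape, ranks and means can lead to different impressions. The article would then report means beside a rank-based p-value, with no rule for which governs the conclusion.

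**Working it through.** **1. Reproduce the plan's figure.** Inputs from Sample size: difference 2, SD 5.69, two-sided alpha 0.05, power 0.80, loss 10%. The allocation is equal ("in a 1:1 allocation ratio by blocks of 4").

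n per arm = 2 × [5.69 × (1.960 + 0.842) / 2]² = 127.06, rounded up to 128. The t-test solution is 128.03.

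After 10% loss: 127.06 / 0.9 = 141.2, or 128 / 0.9 = 142.2.

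The stated 142 agrees. It is therefore an unadjusted two-sample comparison of means, with the loss already included.

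**2. What an interval would add.** With 128 evaluable per arm, the standard error of the difference in means is 5.69 × √(2/128) = 0.71, and the 95% half-width is 1.96 × 0.71 = 1.4 points. Some illustrative results in a comparison of means:

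| Observed difference | 95% CI | Significant at 5%? | Reading against 2 points |
|---|---|---|---|
| 0.5 | −0.9 to 1.9 | no | 2 points excluded |
| 1.0 | −0.4 to 2.4 | no | 2 points not excluded |
| 1.5 | 0.1 to 2.9 | yes | compatible with less or more than 2 |
| 3.5 | 2.1 to 4.9 | yes | above 2 throughout |

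The significance column cannot separate the first row from the second, or the third from the fourth. The interval does.

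**3. Power of the declared test.** For normal scores the Wilcoxon test has asymptotic relative efficiency 3/π = 0.955 against the t-test, so n in the power formula is multiplied by 0.955. The documents give no CAT distribution for this population, so each row rests on an assumption.

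| Assumed scores | Evaluable per arm | Comparison of means | Wilcoxon |
|---|---|---|---|
| Normal | 128 (10% lost) | 80.0% (t), 80.3% (normal approximation) | 78.5% by formula, 78.3% simulated |
| Normal, rounded to whole points | 128 | 79.9% simulated | 78.1% simulated |
| Normal | 142 (none lost) | 83.9% (t) | 82.5% by formula, 82.1% simulated |
| Right-skewed (gamma, control mean 12, SD 5.69 in both arms) | 128 | 80.3% simulated | 88.1% simulated |

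Simulations used 20,000 runs per row.

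For 80% Wilcoxon power with normal scores, 127.06 / 0.955 = 133 evaluable per arm are needed. With 142 randomised per arm, that is met if loss is below about 1 − 133/142 = 6.3%.

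**The case against.** **The article may leave the estimate to the SAP.** The estimator and interval are often set out in the analysis plan or full protocol, which are not shown. Silence alone would be no finding. But the article is not silent on the primary analysis: it names the test, carries the baseline-table statistics over to the outcomes and excludes multivariate models. The mismatch between the sizing quantity and the declared comparison lies in stated text.

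**Wilcoxon is a defensible test.** This stands. CAT is a bounded whole-number score, and under a pure shift the rank test addresses the same shift as a comparison of means. The problem is the missing estimate, not the test as such.

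Three stronger readings are tempting and are not supported:

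- A reader might infer that the stated beta is missed. Wilcoxon power falls to about 78% only if scores are normal and the full 10% is lost. It exceeds 80% with smaller losses, and also under the right-skewed distribution tried. The documents give no basis for choosing among these.
- A reader might infer that the result cannot be read against 2 points at all. Means and SDs per arm are to be reported for outcomes, so a difference follows by subtraction and an approximate interval from the SDs and group sizes. That, however, is a reconstruction after the fact by a method other than the declared test.
- A reader might object that an observed difference of about 1.4 points would already be significant. That is true of any two-sided 5% superiority test with 80% power: significance begins at 1.96 / 2.80 = 0.70 of the design difference, here 1.4 of 2 points. It would hold equally for the analysis recommended below, so it is no defect of this plan.

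**Conclusion.** The point holds as a mismatch between what the trial was sized to detect and what the declared primary analysis delivers. As written, the conclusion rests on a rank-test p-value, with no pre-specified between-group CAT difference or interval to show the size of the effect relative to 2 points.

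The sample size is not in error, and no shortfall in power is claimed. The half-width of 1.4 points rests on the plan's SD of 5.69, taken from stable COPD patients, and on 128 evaluable per arm. The conclusion about the missing estimate depends on neither figure. If an unseen SAP already names an estimate with an interval, what remains is to bring the article's text and the sample size basis into line with it.

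**What to change.** In Statistical analysis, make the between-group difference in mean CAT at day 28, with its 95% CI, the primary result, and report it alongside the 2-point threshold. Preferably adjust it for baseline CAT, which the visit schedule already collects. That requires amending the sentence that excludes multivariate analysis. An unadjusted difference would also cure the main defect and leave that sentence alone.

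If the Wilcoxon test stays primary:

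- add the Hodges-Lehmann shift with its 95% CI;
- state in Sample size that the power given is for a comparison of means;
- give the Wilcoxon power with its conditions: about 78% if scores are normal and 10% are lost, higher if losses are smaller or under a right-skewed distribution such as the one tried.

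The cost is protocol or SAP wording, to be settled before unblinding. The sample size stays at 142 per arm, with no added visits or data collection.

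### The primary comparison of CAT at 4 weeks makes no use of the baseline CAT score and excludes any adjusted model; it is valid, but gives up precision that an ANCOVA would recover at no cost in patients

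*Protocol article*

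**What the plan says.** The Outcomes section states: "The primary outcome is health-related quality of life associated with respiratory symptoms according to the CAT Scale", assessed 4 weeks after the start of treatment. It defines no change from baseline.

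Baseline CAT is available. The day 1 visit description reads: "Investigators will collect the following baseline information: sociodemographic data, clinical data, use of concomitant medication, health-related quality of life", and Table 2 marks CAT at t0 and t1.

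The Statistical analysis section first assigns the Wilcoxon test to quantitative variables when baseline characteristics are compared. It then says of the outcomes: "Outcome measures will be described and compared between the montelukast and placebo groups using the same statistics. No multivariate analysis will be performed". The only further use of a baseline variable in the outcome analysis is a subgroup analysis by symptom duration (below 6 months against 6 months or more).

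Allocation is "without stratification, in a 1:1 allocation ratio by blocks of 4", so the design does not balance baseline CAT between the arms.

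The sample size rests on "a weighted common standard deviation of the CAT score of 5.69 was observed" and concludes that "142 individuals in the treatment group and 142 in the control group are needed to detect a difference of 2 units".

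**The concern.** Patients enter with mMRC dyspnea of 1 to 3 and with symptoms lasting from 4 weeks to 1 year, so CAT can be expected to differ between patients before treatment. To the extent that baseline CAT predicts CAT four weeks later, ignoring it leaves explainable variation in the standard error. The same omission means that a chance difference between the arms at baseline passes in part into the day-28 difference.

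The protocol states this as a choice. It is not a detail left open for an analysis plan: a plan that introduced a covariate would contradict the published text.

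There is a secondary cost. The clinical threshold and the design target are both 2 CAT points, while a Wilcoxon test by itself yields a p-value and not a mean difference in CAT points.

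**Working it through.** **Inputs from the Sample size section.** SD 5.69; difference 2; 142 randomised per arm; "accepting an alpha risk of 0.05 and a beta risk under 0.2 in a two-tailed contrast"; "We assume a 10% loss to follow-up rate".

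**Assumptions not in the documents.** The correlation r between baseline and day-28 CAT, taken from 0.3 to 0.7; a baseline SD equal to 5.69; normality for the Wilcoxon figure.

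**Step 1: reproduce the stated size.** With n per arm = 2 × (z₀.₉₇₅ + z₀.₈₀)² × SD² / difference²:

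2 × (1.960 + 0.842)² × 5.69² / 2² = 127.06 evaluable per arm

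127.06 / 0.9 = 141.2, rounded up to 142.

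The stated figure reproduces. It comes from an unadjusted comparison of two means and already includes the 10% loss.

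**Step 2: power of the planned analysis.** Evaluable per arm: 142 × 0.9 = 127.8. The SE of the difference is 5.69 × √(2/127.8) = 0.712.

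- Two-sample t-test (noncentral t): 79.9%. The normal approximation gives 80.2%.
- Wilcoxon test, at its normal-theory efficiency of 0.955 relative to the t-test (127.8 × 0.955 = 122.0 effective per arm): 78.1% by noncentral t, 78.4% by the normal approximation. Beta is therefore about 0.22.

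**Step 3: power with baseline CAT in the model.** ANCOVA replaces SD by SD × √(1 − r²), so the variance of the estimate falls by the fraction r². Noncentral-t power at 127.8 per arm:

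| Assumed r | Residual SD | SE of difference | Power |
|---|---|---|---|
| 0 (unadjusted) | 5.69 | 0.712 | 79.9% |
| 0.3 | 5.43 | 0.679 | 83.5% |
| 0.4 | 5.22 | 0.652 | 86.3% |
| 0.5 | 4.93 | 0.616 | 89.8% |
| 0.6 | 4.55 | 0.569 | 93.8% |
| 0.7 | 4.06 | 0.508 | 97.5% |

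**Step 4: would a change score do as well?** Its SD is 5.69 × √(2(1 − r)) when the two SDs are equal. Normal-approximation power is 66.1% at r = 0.3, 80.2% at r = 0.5 and 95.2% at r = 0.7, against 83.8%, 90.1% and 97.6% for ANCOVA on the same approximation. Reading the outcome as change from baseline therefore does not remove the point.

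**Step 5: chance imbalance.** With baseline SD 5.69, the SE of the baseline difference is 5.69 × √(2/142) = 0.675 among all randomised, or 0.712 among 127.8 per arm. A difference of 1 point or more in either direction then has probability 2 × [1 − Φ(1/0.675)] = 14%, or 2 × [1 − Φ(1/0.712)] = 16%. With equal SDs at both times the regression slope is r, so a 1-point imbalance shifts the unadjusted day-28 difference by about r points: 0.3 to 0.7, or 15% to 35% of the 2-point target.

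**The case against.** The strongest reply is that nothing here is wrong. In a 1:1 randomised trial the unadjusted comparison controls type I error and is unbiased over repeated randomisations, and the sample size was derived for an unadjusted comparison. That stands. A reader might infer that the primary analysis is biased or the trial wrongly sized; the documents support neither. The shortfall in power is about two percentage points.

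The gain also depends on r, which the documents do not give. Entry restricted to mMRC 1 to 3, without hospitalised patients or chronic lung disease, may narrow the baseline spread and lower r. At r = 0.3 the gain is under 4 percentage points. This too stands, and is why the range starts there.

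Lost precision and chance imbalance are largely one cost seen twice, because random baseline differences are already inside the unadjusted standard error. They should not be added together.

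Further inferences to avoid:

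- That symptom duration is ignored altogether. It defines a planned subgroup analysis, although that is not adjustment.
- That the plan is deficient because it tests baseline comparability without a way to respond. Adjusting only after a baseline test shows imbalance would be poor practice; the case for ANCOVA rests on prespecification.
- That power collapses because the SD in long COVID is larger. The source SD is from COPD, but the document offers no other value.
- That the protocol says in terms that the raw score is tested. This is inferred from the outcome definition; the objective speaks of improving quality of life. Step 4 shows that the point holds on either reading.

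**Conclusion.** The point holds as a recommended improvement. The protocol collects baseline CAT, leaves it out of the primary comparison and excludes the model that would use it. On the protocol's own inputs the planned Wilcoxon test has about 78% power under normality, slightly below the 80% implied by its beta. ANCOVA with the same patients would have about 83% to 97% for r between 0.3 and 0.7. If the baseline SD is also 5.69, roughly one trial in six or seven would show a baseline difference of at least 1 point, moving the unadjusted estimate by about 0.3 to 0.7 points.

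The direction of the gain does not depend on which r in this range is true, but its size does. A reader might conclude from the upper end of the range that the plan cannot stand without the change. It can: the analysis as written is valid and close to its power target.

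**What to change.** Before unblinding, replace the sentence that excludes multivariate analysis with wording such as:

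> *The primary analysis is an ANCOVA of day-28 CAT on treatment and baseline CAT, reporting the adjusted mean difference with 95% CI. Secondary quantitative outcomes with a baseline measurement are adjusted for that baseline.*

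Keep the Wilcoxon test as a sensitivity analysis and the sample size at 284. Adjusting for symptom duration as well is optional; its extra gain cannot be quantified from the document.

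No new data and no further patients are needed. The cost is a short amendment which, if judged relevant under the Ethics and dissemination section, must go to the ethics committee and/or the medicines agency, with the change communicated to the registries. The timing matters: the same adjustment introduced after unblinding would be post hoc and would contradict the published plan.
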